## Abstract

**Background:**

Disruptive behavior is a common reason for young children to be referred to mental health care services worldwide. Research indicates that treatments for child disruptive behavior where parents are the primary agents of change are most impactful. Parent-Child Interaction Therapy (PCIT) is an effective parent management training program currently implemented in therapeutic settings within the Netherlands. Ongoing research into improving the effectiveness of PCIT is being done within these settings. To further promote the key elements of PCIT, this study focuses on creating the opportunity for parents to practice positive parenting skills more outside of the clinical setting by adding virtual reality (VR) as an additional homework element. PCIT has shown to make impactful long-term improvements in parental warmth, responsiveness, and the parent-child relationship. Through VR, parents practice the taught parenting skills out loud in the comfort of their own homes in VR scenarios. We expect that VR addition will innovatively increase the effectiveness of PCIT.

**Objective:**

This study aimed to evaluate the added value of VR to PCIT by using a multiple baseline single-case experimental design (SCED). We expect to find that PCIT-VR will ameliorate positive parenting skills. By implementing the VR element, we secondarily expected that meeting the skill criteria will be achieved sooner, treatment completion rates will increase, and the parent-child relationship will be better, whereas parental stress and child disruptive behavior will decrease.

**Methods:**

A total of 15 children (aged 2-7 years) with disruptive behavior and their parents will be followed throughout the PCIT-VR treatment. Using a multiple baseline SCED with 3 phases, 15 families will fill out questionnaires weekly, in addition to having pre- and posttreatment and follow-up measurements to monitor their positive parenting skills, child disruptive behavior, parenting stress, and VR progress. Moreover, quantitative information and qualitative interviews will be analyzed visually and statistically and summarized to provide a complete picture of experiences.

**Results:**

As of February 2021, 6 families have been enrolled in the study at the moment of submission. Data collection is projected to be completed in 2023. Quantitative and qualitative results are planned to be published in peer-reviewed journals, as well as being presented at national and international conferences.

**Conclusions:**

The SCED—with its phased design, randomization, and the opportunity to replicate and assess both individual and group treatment effects—and adaptability of the VR technology are the strengths of the study. The risks of increased type I errors, maturation effects, or technological failure will be mitigated with the right statistical support. This study aims to magnify the scope of the treatment through additional skill training, ultimately in support of routinely implementing VR within PCIT.

**International Registered Report Identifier (IRRID):**

DERR1-10.2196/34120

## Introduction

### Background

Disruptive behavior is one of the most frequent reasons for young children to be referred to child and adolescent mental health care services worldwide [1]. Statistics show that of the population in the United States, 7% to 9% of children have a diagnosed behavioral problem [2], and in Western culture, there is an increase in the prevalence of behavioral problems [3]. Behavioral problems at a young age have an effect on the child, as well as on his or her surroundings and society at large [4,5]. The long-term effects of untreated, externalizing, disruptive behavior includes school dropouts, peer rejection, developing antisocial personality disorders, higher public costs for health care and education, and both nonviolent and violent delinquency and criminality in adulthood [6-10]. However, protective factors include enhancing prosocial skills for children and fostering the mental well-being of parents [11]. Therefore, to prevent child disruptive behavior or intervene at an early stage, children need evidence-based programs that focus on ameliorating parental skills and diminishing child disruptive behavior. Research concludes that treatments for child disruptive behavior where parents are the primary agents of change have the most substantive evidence for effectiveness [12].

There are currently a few parent management training (PMT) programs that focus on improving parent-child interactions, which are being implemented worldwide [13]. Importantly, parenting is fundamentally linked to children developing life skills, and worldwide research into parenting programs has shown that developmental, emotional, behavioral, and health outcomes for both parents and children can improve as a result [14]. Within PMT programs, research has shown that programs based on the social learning theory are the most effective [12], of which Parent-Child Interaction Therapy (PCIT) is one [15]. PCIT is an evidence-based treatment that focuses on diminishing externalizing disruptive child behavior by strengthening parenting skills [16]. The therapy, where parents and children play together throughout a session, distinguishes itself from most other PMT programs through live coaching from the therapist, which focuses on increasing positive parenting skills [17].

PCIT has been well-researched pan culturally, with effect sizes varying between 49% and 59% [18]. Specifically in the Netherlands, PCIT has also been shown to be effective with higher effect sizes in a randomized controlled trial (RCT) comparing PCIT with a 10- to 15-session care as usual treatment (family creative therapy) available in the community mental health setting (mean 45.4, SD 3.6, for PCIT vs mean 34.0, SD 4.93 for family creative therapy; t_23_=6.25; *P*<.001) [19]. Although these effect sizes indicate that PCIT is an effective treatment, this study aims to focus on the gains that can still be achieved by allowing more families to benefit from PCIT by increasing the effect sizes, accessibility, and impact of the treatment by focusing on strengthening positive parenting skills.

Worldwide, dropout rates vary between 12% and 67% [20], and specifically in the Netherlands, studies indicate that there is high attrition and that parents have a hard time grasping the different parenting skills. In that study, 52% of parents who received PCIT dropped out [19]. Attrition rates worldwide seem to be attributed to parenting stress levels and treatment barriers [20]. For instance, single parent status, problem severity of the child, and low socioeconomic status are often attributed to attrition. However, there remains some discrepancy in the literature on what factors contribute to families dropping out, although many studies have attempted to identify predictive factors [21-23]. Nonetheless, one study found that treatment completers reported significantly fewer child behavioral problems and less parental stress at follow-up than treatment dropouts [24]. This indicates that treatment should focus on making parents feel more confident in their parenting, thus potentially diminishing parenting stress and, with that, dropout rates. In further support, a study found that treatment completers showed increasing positive parenting skills and decreasing negative parenting skills from before to after treatment [21]. In addition, positive parenting skills appear to be crucial for improving the parent-child relationship [7]. A meta-analysis on PCIT showed that when meeting the skill criteria is required for completion of treatment, child externalizing behavior is significantly lower than when this is not a requirement [18]. However, when PCIT is offered in a shorter form in community samples (eg, the *standard* 12-session PCIT or the 8-session PCIT-Home), comparable effect sizes can still be yielded for a reduction in disruptive behavior [18,25]. Nonetheless, if skill criteria are met when taking the traditional PCIT protocol into account, PCIT has been shown to make impactful long-term improvements in parental warmth, responsiveness, and effectiveness [17]. In addition, studies have shown that the performance and motivation of a skill can be improved by deliberately practicing that skill [26]. Moreover, parenting programs that incorporate the opportunity to practice new skills with their children are considered more effective interventions than those that do not [27,28]. This suggests that it could be beneficial for parents to practice the skills they learn in the therapy more intensely, thereby potentially reducing dropouts and magnifying the scope of the treatment. It has previously been shown that with live coaching feedback, positive parenting skills increase rapidly, whereas negative parenting behavior decreases rapidly, especially early in the intervention. These results indicate that early interaction change in positive parenting skill acquisition is related to more positive child welfare outcomes [29]. In addition, research indicates that a current obstacle in PCIT is that parents may have a hard time grasping parenting skills, which leads them to drop out because of the inability to fully understand and translate the parenting skills to their home setting [19]. Therefore, to bridge the gap between practicing the (Praise, Reflect, Imitate, Describe, and Enthusiasm [PRIDE]) skills in therapy and applying the skills in a home setting, this study will implement a virtual reality (VR) element. VR allows parents to practice skills regardless of whether their child is home or awake, meaning that the ability to practice skills is on demand whenever they have their smartphone device near them. Over the past years, VR has become increasingly popular within the mental health care sector, as it creates opportunities that would otherwise not be possible [30]. Thus far, research has shown that using technology in PMT programs maintains positive treatment outcomes as long as therapist contact is maintained [31]. Specifically, within PCIT, previously implemented technology augmentations, such as Pocket-PCIT, have been shown to lead to increased treatment completion rates. This indicates a promising development in using technology innovations in an attempt to tackle similar barriers to treatment engagement [28].

VR offers multiple advantages in the field of psychological research. First, a stimulus can be presented in 3 dimensions [30]. Second, a virtual environment can be manipulated and controlled to create scenarios for participants, whereas in a real-world environment, there are always variables present that cannot be controlled [32]. Third, VR technology is designed for immersion, meaning that the created virtual world becomes the real world for a moment [33]. Clearly, VR is an experience generator that opens up possibilities for creating experiences that would otherwise not be possible [33]. Thus far, in psychology and psychiatry, VR has been an effective tool in the treatment of anxiety disorders, posttraumatic stress disorder, schizophrenia, eating disorders, and substance abuse disorders [34]. It is most commonly used in exposure-based therapy and behavioral skills training [35]. Considering this study, we will focus on the use of VR for the behavioral skills training of parents. The goal is to teach certain skills to be applied in multiple environments [36]. When using VR for behavioral skills training in this study, the goal is to create an environment where the parent can additionally practice skills that they find difficult to use in the parent-child interaction. A study on the development of mindfulness skills for borderline personality disorder has shown that practicing mindfulness within a virtual environment creates the opportunity to generalize the skills to the natural context outside of therapy [37]. In addition, it has also been shown that practicing and training skills for dangerous situations, such as fire hazards in a virtual environment, are also effective [36]. These studies are precedents of how it is possible to apply VR to practice and train skills in a virtual environment. Thus, this study aims to implement VR as a low-threshold opportunity for parents to practice the skills they are taught in therapy, on their own time, within the context of their own home.

To date, no study has implemented VR to improve positive parenting skills in PCIT or in other PMT programs, although passive technological augmentations have been successful thus far [28,31]. However, considering that studies indicate that a current attrition obstacle in PCIT is that parents may have a hard time grasping the parenting skills, the addition of VR as a tool to practice skills, which can be generalized to a person’s natural context, seems to be a good addition to the therapy. Nonetheless, research suggests that VR should and could, in no way, replace the clinician but rather should be integrated into the therapy to augment the intervention [38]. Therefore, the implementation of VR in PCIT creates an accessible platform for parents to further grasp positive parenting skills, thus increasing the potential for PCIT to have an impactful and lasting effect. Consequently, rather than VR being an additional layer of homework—and thus an additional life stressor—it may, in fact, alleviate parents as their ability to practice skills is essentially always *on demand*. The research group involved in this project previously tested this VR concept for PCIT with a test 360° video showing the PCIT skills [39]. This was consequently evaluated by PCIT therapists and researchers. All therapists and researchers were enthusiastic about the prospect of adding this VR element to the therapy, creating an additional opportunity for parents to practice [39]. For example, if parents are divorced and do not always have their child with them, they can practice their parenting skills nonetheless through VR. Although a double-blind RCT might be feasible in PCIT, there are significant limitations to implementing this design in clinical practice. For example, it is difficult to include a sufficiently large study population to say something meaningful about the additional VR element in clinical practice. Instead, we have chosen to use an innovative trial design, the multiple baseline single-case experimental design (SCED). This design will enable all participants to benefit from the additional VR element, which will consequently improve the power of the study compared with a traditional RCT. The design is further explained in the *Study Design* section. Therefore, the purpose of implementing PCIT-VR is to provide all parents with an easy opportunity to solidify their positive parenting skills in the comfort of their own homes.

### Aims

The primary goal of this research project is to evaluate the implementation of VR in PCIT. We expect to find that PCIT-VR will ameliorate positive parenting skills, leading to faster achievement of the meeting of skill criteria. We believe that if positive parenting skills are trained more frequently by implementing the VR element, additional effects will also take place, such as achieving child-directed interaction (CDI) skill criteria sooner than when not using VR and increasing the treatment completion rate. We expect that by implementing a VR element, parents benefit from more intensive training, and VR will additionally innovatively magnify the scope of families (eg, split families with separated parents) who can benefit from PCIT. In addition, parental stress, child disruptive behavior, and analytics of VR will be secondarily measured.

As a whole, PCIT-VR is developed as an augmented version of PCIT, where the focus lies on ensuring that parents practice and learn positive parenting skills intensely. This is achieved by incorporating practicing with VR as an integral part of the therapy. The threshold for practicing skills at home using VR is low, as parents are simply able to use their smartphone devices. PCIT-VR creates the opportunity for parents to practice and become familiar with the skills they have been taught in the therapy sessions in the comfort of their own homes. The implementation of VR functions as additional *skill training*. Providing families with PCIT-VR at an early age and early stage can potentially prevent them from needing more intensive help at a later stage and can possibly minimize the impact of child disruptive behavior, not only in the long run but also during the therapy itself.

Secondary objectives are the effects that we expect because of the overall amelioration of positive parenting skills that cause both parental stress and child disruptive behavior to diminish. Therefore, we expect that the total number of PCIT sessions will diminish and that the overall completion of treatment will increase. In addition, family dynamics and competencies will be secondarily measured, meaning that we will be able to evaluate parental compliance in the use of VR and evaluate potential risk factors for dropout. We believe that parents choosing to use VR will show higher levels of compliance as they want to use an additional tool to learn the skills. Secondary objectives also include positive VR experiences and general therapy satisfaction. Furthermore, we expect that PCIT-VR will secondarily lead to a better quality of parent-child relationships. We expect that the effects of PCIT-VR are further maintained and engrained in the long term because of the additional skill training provided by the VR scenarios.

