## Methods

### Participants

Children (aged 2-7 years) and their parents will be referred through community channels after seeking help or support. The research will be conducted in clinical practice in the Netherlands, where families first follow a standard intake procedure (which includes an intake interview, completion of a set of questionnaires, and being referred to the right area of expertise) to establish their need for help. After this, families can be included in the study and receive PCIT-VR if the following criteria are met:

Disruptive behavior problems of the child are a reason for referralChildren are aged between 2 and 7 yearsParents speak Dutch or English

A total of 15 families will be included, preferably those who finish the treatment (including all treatment phases and measurement points).

As the design is a SCED, the calculations for the number of participants are based on the What Works Clearinghouse (WWC) [40] and information gained from previous PCIT research. The WWC standards dictate that there are 5 criteria that should be acknowledged in a SCED. One of these criteria states that the minimum number of participants necessary to demonstrate an intervention effect is 3 [41]. In addition, the American Psychological Association [42] states that to display the effectiveness of an intervention, a minimum of 9 replicated single-case studies should be performed. Furthermore, attrition rates according to the standard PCIT ranged between 34% and 77% [43]. Specifically, in the Netherlands, a previous study showed a 40% attrition rate [19]. Therefore, this study will strive to include 15 families, preferably those who finish the entire trajectory to (1) adhere to a minimum of 3 participants according to WWC standards, (2) be able to state that the intervention is effective in accordance with the American Psychological Association guidelines, and (3) compensate for the potential of a 40% attrition rate.

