The multiple baseline SCED in this study is set up as shown in Figure 1. First, informed consent will be signed after families have received verbal and written information about the study. Second, participants will be dually randomized (by an external party) to determine their baseline period (4, 5, or 6 weeks of baseline measurements; phase A) and the addition of their VR element (VR at the start of CDI and after 3 or 6 sessions of CDI; phase B). After randomization, participants will start with phase A—the baseline period. Parents will electronically fill out the questionnaires weekly regarding child disruptive behaviors and parental stress using the ECBI and the short version of the OBVL. At the end of phase A, a pretreatment assessment will be performed. In this assessment, parents will be required to electronically fill out more questionnaires regarding both child and parental factors (Figure 1; see the *Assessment Instruments* section). In addition, the researcher will also make a video recording of the parent and child playing in 3 play situations (child-led play [CLP], parent-led play [PLP], and clean up [CU]), which will consequently be coded using the Dyadic Parent-Child Interaction Coding System (DPICS) [52]. Following this, in phase B, the intervention phase starts. Depending on their random allocation, families will start off with PCIT with or without the VR element. Once again, they will electronically fill out the ECBI and OBVL-*kort* (OBVL-K) weekly, and they will also register their homework completion and (if applicable) their VR completion sheets. During the PCIT sessions, PCIT therapists will register the parental progress weekly by coding 5 minutes of playtime with the DPICS. Once families reach CDI completion, they will move on to phase C, which is the parent-directed interaction (PDI) phase of PCIT. Measurements in phase C are identical to those in phase B. After treatment completion, a posttreatment assessment will be performed, which will be identical to the pretreatment assessment. Phase D is the follow-up assessment, which takes place 6 months after treatment completion. The assessment is also identical to the pre- and posttreatment assessments (Figure 2; 10 CDI sessions and 6 PDI sessions are used as a random example).

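### Total sessions and treatment completion have no no-VR reference, and reaching CDI criteria sooner can be addressed only through the small randomised VR-start contrast

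*Protocol article*

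**What the plan says.** The Aims section of the protocol article states comparative expectations. VR should lead to "achieving child-directed interaction (CDI) skill criteria sooner than when not using VR and increasing the treatment completion rate". Later in the same section: "we expect that the total number of PCIT sessions will diminish and that the overall completion of treatment will increase". Principal Findings, in the Discussion, repeats the expectation of fewer sessions and lower dropout.

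On who receives VR, the Background says: "This design will enable all participants to benefit from the additional VR element". Study Design randomises two things: the baseline length (4, 5 or 6 weeks) and the point at which VR is added ("VR at the start of CDI and after 3 or 6 sessions of CDI; phase B"). No family is assigned PCIT without VR throughout.

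On numbers, Participants says: "A total of 15 families will be included, preferably those who finish the treatment". The size rests on a guideline that "a minimum of 9 replicated single-case studies should be performed" and on a wish to "compensate for the potential of a 40% attrition rate". The attrition figures serve as background and as support for the sample size. They are not set as a benchmark for completion.

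**The concern.** A single-case design estimates an effect by comparing repeated measurements on the same family across phases. That works for the weekly therapist-coded DPICS, the ECBI and the OBVL-K. It does not work for total sessions or completion, because each family gives only one value, at the end of treatment. By then every family that stayed long enough has been given VR. Words such as fewer and increased need a reference, and for these two outcomes the article names none, whether an arm, a phase or an outside cohort.

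Without a restatement, a claim that VR shortened treatment or raised completion would rest on an uncontrolled series of 15 families. The stated preference for families who finish could itself raise the observed completion rate if it affected who is counted.

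The CDI-criteria aim is different, because the staggered start supplies a randomised comparison. The article describes that comparison only for acquired skills (Discussion, Principal Findings) and does not link it to time to criteria.

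**Working it through.** **Reproducing the plan's figure.** Inputs from Participants: 9 replications and 40% attrition. 9 / (1 − 0.40) = 15, which matches. The size therefore comes from a replication count and attrition. No effect size or power is stated for any comparison.

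**What comparator each outcome has.**

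| Outcome | Values per family | Comparator in the design |
|---|---|---|
| Weekly DPICS, ECBI, OBVL-K | many | within-family phases, plus staggered VR start |
| Sessions to CDI criteria | one | randomised VR start: both delayed groups are VR-free in sessions 1–3, the after-6 group also in sessions 4–6 |
| Total sessions | one | none without VR; the start groups differ only in when VR came |
| Completion | one | none without VR; as above |

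In the article's illustrative course (10 CDI and 6 PDI sessions), the VR-free share of CDI is 0/10, 3/10 and 6/10 in the three groups. Of the whole course of 16 sessions, it is at most 6.

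**How much the randomised contrast can show.** I assume an even split of 5/5/5 and two-sided 0.05.
- Sessions, 5 vs 5, normal approximation (optimistic at this size): power is 24% at a difference of 0.8 SD, 35% at 1.0 SD and 81% at 1.8 SD.
- Completion, Fisher exact test, 60% in the delayed families and 80%, 90% or 100% in the early ones: power is 3%, 6% and 9% for 5 vs 5, and 6%, 10% and 17% for 5 vs 10.
- For scale, a parallel no-VR arm would need about 82 families per arm to detect 60% vs 80% completion.

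**How completion would read against an outside rate.** The article gives two attrition figures for the same cited Dutch study: 40% in Participants and 52% in the Background. The implied completion rates are 1 − 0.40 = 60% and 1 − 0.52 = 48%. Exact (Clopper-Pearson) 95% intervals and one-sided binomial p-values for 15 families:

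| Completers | 95% interval | p vs 60% | p vs 48% |
|---|---|---|---|
| 9 | 32.3%–83.7% | 0.610 | 0.251 |
| 11 | 44.9%–92.2% | 0.217 | 0.043 |
| 12 | 51.9%–95.7% | 0.091 | 0.012 |
| 13 | 59.5%–98.3% | 0.027 | 0.002 |
| 14 | 68.1%–99.8% | 0.005 | <0.001 |

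With a two-sided interval, 14 completers are needed to exclude 60% but only 12 to exclude 48%. With a one-sided 0.05 test, the counts are 13 and 11. At a true completion of 80%, the power of the one-sided test is 40% against 60% and 84% against 48%. The answer depends on which outside figure and which test are chosen, and the article fixes neither.

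**The case against.** The strongest reply is that the design does contain a comparator. The delayed families have 3 or 6 randomised VR-free sessions, so reaching CDI criteria within that window is a true VR versus no-VR contrast. This stands. A reader might infer that none of the comparative aims can be tested because all families get VR. For the CDI-criteria aim the article does not support that reading; the limitation there is precision and a short window. The reply does not extend to total sessions or overall completion, which are settled only after the groups have all been offered VR.

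Two other tempting readings also fail. One is that the phrase "parents choosing to use VR will show higher levels of compliance" contradicts allocation. VR is allocated, but its use at home varies and is logged (VR Implementation, VR User Analytics, VR Completion), so the phrase can mean measured uptake. The other is that families will be grouped by the VR they actually received, which would build long CDI into the late group. No section proposes this.

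It is also fair to say that these are expectations in a condensed article and that Statistical Analysis commits to no confirmatory test of them. An analysis plan could add detail, but it could not create a no-VR arm. The primary skills question is unaffected.

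**Conclusion.** The point holds for total sessions and completion: zero of 15 families is assigned PCIT without VR, each outcome occurs once per family, and no outside reference is set. The trial can describe these outcomes but cannot attribute a change in them to VR. For sessions to CDI criteria, a randomised early-versus-delayed comparison exists. With about 5 families per group it would reach about 80% power only near a 1.8 SD difference.

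The power figures rest on an even split, which the article does not state, and on assumed completion rates. The interval thresholds depend on the benchmark: a reader might take 14 of 15 as the bar for an increase, but that applies only to the 60% rate with a two-sided interval.

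**What to change.** 1. Restate the CDI-criteria aim as sessions to criteria compared across the three randomised VR-start groups. Keep each family in its randomised group even if it meets criteria or drops out before VR begins. Count dropouts as not having reached criteria (for example, censored at their last session), and say which rule is used. Report an estimate with its interval.
2. Report total sessions and completion descriptively. Give completion an exact confidence interval over all enrolled families, not only those who finish, and make no claim of an increase or reduction due to VR.
3. If an outside attrition rate is quoted for context, first reconcile the 40% and 52% given for the same Dutch study.

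The cost is rewording the aims and one added summary by randomised group, with no change to recruitment, treatment or data collection. The secondary claims become weaker, and the one randomised contrast will be imprecise.
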